### Allocation procedures

Randomization will be by practice. The study will compare the use of the decision aids within the clinical encounter versus usual care. We will identify pairs of practices that are most similar in size (i.e., number of clinicians seeing adult patients with type 2 diabetes) and randomize within each pair to use either the 1) the *Statin Choice* and the *Aspirin Choice*, or 2) the *Diabetes Medication Choice* decision aid. Each practice will also serve as the usual care arm for the other intervention arm (Figure 2). This approach will seek to ensure similar representation of ‘easy’ and ‘difficult’ practices in both decision aid groups and eliminate the need for any site to simply serve as a usual care arm. A study statistician will perform the randomization centrally after the practices have been enrolled, ensuring concealment of allocation of the paired practices. Practices, clinicians, patients, and investigators will not be masked to the intervention. However, patients providing outcomes will remain masked to their practice status, as consent documents will keep patients unaware of the study’s main hypotheses. Furthermore, we will centrally follow patients and ensure that patient surveys and pharmacy follow-up are completed according to the intention-to-treat principle.

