##### Sample size

A total of 8 practices will be randomized to 1) the Diabetes Medication Choice decision aid plus statin and aspirin usual care or 2) the Statin Choice and Aspirin Choice decision aids plus diabetes medication usual care. The Statin Choice cluster randomized trial evaluated decision quality comparing the decision aid to usual care. This study reported a 9.8 point difference in decision quality^3^ with the standard deviation of 16.9 and 14.1 for the usual care and decision aid groups, respectively. Making the following assumptions: 1) variances are as reported in this study; 2) we seek to detect a difference of 9.8 points or greater in decision quality between two groups at significance level of 0.05, with a two-sided *t*-test; 3) a modest correlation of outcomes across these clinicians and practices (which is a conservative assumption) represented by an intracluster correlation coefficient (ICC = between cluster variance/total variance) of 0.05; 4) a variance inflation or design effect factor [1+ (n − 1) · ICC], where n is the number of patients per cluster [31]; and 5) an approximated 20% attrition rate, we will have 80% power if we are able to recruit 30 patients per clinic for a total recruitment target of 240 patients. Assuming a similar ICC and attrition rate for other outcomes, this sample size will have 99% power to detect a 1 SD difference in any continuous measure (e.g., approximately a 2-point difference in a 10-question knowledge scale), and 80% power to detect a 30% difference in 6-month adherence rates assuming a control adherence rate of 50%. Actual power will be likely greater because we will adjust for baseline values and characteristics and because of our conservative assumptions.

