##### Analysis

We will have a summary of the cluster level and patient level characteristics within each trial arm, providing counts and frequencies for categorical variables and means with ranges for continuous variables. Because of the uncertainty as to the ability of a cluster trial to create uniform prognostic groups, we will test the null hypothesis of no difference between arms in baseline cluster level characteristics using the weighted paired *t*-test [32]. This test can account for the small number of clusters and an unequal number of patients within each cluster.

To account for the modified study design (e.g., each arm being both intervention and usual care), the study team assumes similar adherence rates within statin medications and diabetes medications along with similar knowledge, decisional conflict, and satisfaction rates for patients discussing either medication for those within the usual care group. For the decision aids (Statin, Aspirin and Diabetes Medication) the study team assumes the same impact on all of these outcomes for all decision aids. With these assumptions, all patients that use a decision aid during the encounter of interest will be grouped in the decision aid arm and those that do not will be grouped under the usual care arm. To account for differences that may exist between the diabetes, statin, and aspirin patients, all models will be adjusted by group. Interaction between arm and group will be tested for significance, recognizing that the study will be underpowered to test for this interaction.

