To evaluate the efficacy of the intervention, differences in all patient level outcomes, for both continuous and dichotomous outcomes (as well as patient characteristics at baseline) will be estimated using the random effects meta-analysis method [31]. This approach has been validated for matched pair cluster-based studies: differences in means for continuous outcomes and in proportions for dichotomous outcomes are estimated and then pooled across strata. A stratum in terms of a matched-pair study is considered to be each pair, and in this trial there are 5 strata. For each outcome, we will thus estimate the effect size and its precision (e.g., 95% confidence interval). The outcomes will be assessed at baseline, 3 and 6 months. We will estimate the intraclass correlation coefficient for each outcome along with its 95% confidence interval and report these for informational purposes only since the number of clusters is insufficient to determine with confidence a true intraclass correlation^124^. Within patients that had a diabetes medication discussion, HbA1c will be collected and categorized to <7.3 versus ≥7.3. This outcome will be analyzed as described above for categorical outcomes. All analysis and data management will be conducted utilizing SAS (version 9, Cary, NC) with use of Stata statistical software (version 11.0, College Station, Tx) for primary endpoint analysis.

Patients with missing outcome data will not be included in assessment of that particular outcome. We will compare the incidence of missing data for each outcome between study arms, both absolutely and as a function of follow-up period. We will report rates of missing data for each outcome by study arm and known reasons for missing data. In the event that the rate of missing data is not independent of study arm or is greater than the assumed 10% loss to follow-up, we will conduct sensitivity analyses under a range of assumptions about the missing values and assess consistency of results across those scenarios. In the event that patients are missing baseline characteristics data, which are otherwise imbalanced between the two study groups, we will use imputations to estimate models which include those characteristics.

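### Random-effects pooling over four (or five) practice pairs is specified without a small-sample interval; in its conventional form the 5% test runs at about 9–10% under the plan's planning model and about 4–8% for the pooled contrast

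*Protocol article*

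**What the plan says.** The Analysis section for Aim 1 sends every patient-level outcome, continuous or dichotomous, to one method: differences between arms "will be estimated using the random effects meta-analysis method [31", computed within each matched pair and then pooled, with a 95% confidence interval. The stated reason is that "This approach has been validated for matched pair cluster-based studies".

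On the number of pairs the document disagrees with itself. The Sample size section says "A total of 8 practices will be randomized", and Allocation procedures says the plan is to "randomize within each pair to use either the 1" of two decision-aid packages, which gives four pairs. The Analysis section says "in this trial there are 5 strata".

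Two other statements bear on the point. ICCs are to be reported for information only, because "the number of clusters is insufficient to determine with confidence a true intraclass correlation". For baseline cluster-level characteristics the section chooses a weighted paired t-test because "This test can account for the small number of clusters and an unequal number of patients within each cluster". No comparable small-sample provision is attached to the outcome analysis.

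Allocation procedures also says "Each practice will also serve as the usual care arm for the other intervention arm", so a practice contributes decision-aid patients on one topic and usual-care patients on the other.

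**The concern.** A random-effects interval needs an estimate of the between-pair variance. With four pairs that estimate has 3 degrees of freedom. The conventional procedure sets it to zero when it comes out negative, then treats it as known and uses 1.96. When it is zero, the standard error reflects patient-level variation only and clustering drops out of the analysis. The result is an interval labelled 95% that covers less often, and a test that rejects too often. The choice of interval could decide whether the primary outcome, decisional conflict, is called different between arms.

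**Working it through.** **Inputs (Sample size section).** Difference 9.8 points; SDs 16.9 and 14.1; ICC 0.05; two-sided 0.05; 30 patients per practice; 20% attrition, so 30 × 0.8 = 24 evaluable; 8 practices.

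**Reproducing the plan's power.** Root-mean-square SD = √[(16.9² + 14.1²)/2] = √(484.42/2) = 15.56. Without clustering, 40 patients per arm are needed. The design effect is 1 + 29 × 0.05 = 2.45, so 40 × 2.45 = 98 per arm, 196 in total, and 196/0.8 = 245 against the stated 240. Conversely, 96 evaluable per arm divided by 2.45 is 39.2, which gives 79.6% power. The stated 80% is reproduced. The calculation treats each practice as single-arm and does not allow for having only 3 or 4 degrees of freedom between pairs.

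**Variance of one pair difference in that model.** Between-practice part: 0.05 × 484.42 = 24.2. Within-practice part: 0.95 × 484.42/24 = 19.2. Total: 43.4. The true standard error over four pairs is √(43.4/4) = 3.29. If the between-pair variance is set to zero, the standard error used is about √(19.2/4) = 2.19, two thirds of the true value.

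**Simulation, single-arm practices.** No true effect, normal outcomes, 24 evaluable per practice, DerSimonian-Laird estimate with 1.96:

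| ICC | Type I error, 4 pairs | Type I error, 5 pairs |
|---|---|---|
| 0 | 4.3% | 4.3% |
| 0.01 | 5.8% | 5.9% |
| 0.05 | 10.2% | 9.3% |
| 0.10 | 12.2% | 10.9% |

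At ICC 0.05 the between-pair variance is estimated as exactly zero in 27% of trials with four pairs and 22% with five. In the zero-estimate trials with four pairs, about 20% reject falsely. Unequal practice sizes (coefficient of variation 0.5) change coverage by less than half a percentage point. Hartung-Knapp and the paired t-test, both on (pairs − 1) df, stay at about 5% with equal practice sizes; with unequal sizes Hartung-Knapp is at most 5.7%.

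**Simulation, each practice split equally between arms (12 + 12).** ICC 0.05, same conventional interval:

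| Practice variance | 4 pairs | 5 pairs |
|---|---|---|
| All specific to topic or arm | 7.6% | 7.8% |
| Half shared within the practice | 6.0% | 6.0% |
| All shared, so it cancels | 4.2% | 4.2% |

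At ICC 0.10 with four pairs the same rows give 10.1%, 7.6% and 4.1%. Hartung-Knapp stays between 5.0% and 5.3% throughout.

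**Effect of a valid interval on width and power (single-arm model, ICC 0.05).** The t quantile is 3.18 on 3 df or 2.78 on 4 df, against 1.96. Median interval width rises from 11.4 to 18.5 points with four pairs, and from 10.6 to 14.9 with five. With four pairs the noncentrality is 9.8/3.29 = 2.98, and power on 3 df is 53%; the conventional analysis rejects in 82% of such trials. With five pairs it is 9.8/√(43.4/5) = 3.33, and power on 4 df is about 70%. That last figure assumes ten practices of 30, or 300 patients. With 240 patients over ten practices (19.2 evaluable each) the pair variance is 24.2 + 0.95 × 484.42/19.2 = 48.2, the noncentrality is 9.8/√(48.2/5) = 3.16, and power is about 66%.

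**The case against.** The strongest objection is that the faulty step is not in the text. The protocol article names no estimator, truncation rule or normal quantile, and a Hartung-Knapp interval is itself a random-effects meta-analysis interval. A full protocol or SAP that is not shown could contain it, and the cited validation cannot be examined here. This stands as a limit on certainty: the inflation belongs to the conventional form, which is the natural reading of the unqualified wording but not a stated choice. It does not remove the point, because the article fixes the method for all patient-level outcomes at a number of pairs where the form of the interval decides whether it is valid.

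Second, the figure near 10% describes practices that each sit in one arm, whereas the pooled analysis puts each practice in both. This also stands. A reader might infer that every planned interval is too narrow; for the pooled contrast the conventional interval ranges from moderately anticonservative to slightly conservative. The single-arm layout remains relevant because the power statement uses it, and because the HbA1c outcome is restricted to patients with a diabetes-medication discussion.

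Third, a reader might take the weighted paired t-test at baseline as proof that the plan contradicts itself. It does not: that test is applied to cluster-level characteristics and the pooling to patient-level data, and the remark about too few clusters concerns reporting of ICCs. Both show awareness of the small number of clusters, no more.

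Fourth, the abstract describes a preliminary estimate. That lowers the stakes of a significance test but not the need for an interval with its stated coverage.

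**Conclusion.** The point holds in a limited form. Random-effects pooling over four or five pairs, read conventionally, gives a type I error of about 9–10% at the plan's ICC of 0.05 in its single-arm planning model, and about 4–8% for the pooled contrast with both arms in each practice. With an ICC near zero there is no inflation. These sizes rest on assumptions the document does not state: the DerSimonian-Laird estimator with a normal quantile, normally distributed outcomes, and an equal split between arms in the second layout. The documents do not support the stronger statement that the error rate is doubled for the primary and every secondary outcome. The mismatch between eight practices and five strata is a plain inconsistency, and it matters here because it sets the degrees of freedom.

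**What to change.** 1. Reconcile the number of pairs between the Sample size, Allocation procedures and Analysis sections.
2. State in the Analysis section that effects on patient-level outcomes are tested and given intervals with a t reference on (pairs − 1) degrees of freedom. Use either Hartung-Knapp or a paired t-test on pair-level differences that are first adjusted for group and baseline as already planned. Replacing 1.96 by the t quantile while keeping the conventional standard error is not equivalent: with four pairs at ICC 0.05 it covers 98.6%.
3. Keep the normal-quantile random-effects result as a sensitivity analysis.
4. Restate the 80% power on this basis, with enrolment unchanged: about 53% with four pairs under the single-arm planning model. With five pairs it is about 70% at 30 patients per practice, or about 66% if the total stays at 240.

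No new data are needed. The cost is a few sentences of text, a first-stage adjustment if the paired t-test is chosen, wider intervals and a lower stated power. The change should be made before outcome data are seen.

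### The plan promises adjustment by topic in all models, but the pair-level efficacy estimator it describes has no place for topic; the two paragraphs need reconciling

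*Protocol article*

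**What the plan says.** Allocation procedures in the Protocol article sets up the pairs: "We will identify pairs of practices that are most similar in size". Within a pair, one practice is randomised to the diabetes medication aid and the other to the statin and aspirin aids. The same section adds: "Each practice will also serve as the usual care arm for the other intervention arm".

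The Aim 1 Analysis section then merges the topics: "all patients that use a decision aid during the encounter of interest will be grouped in the decision aid arm", and everyone else goes to usual care. Two assumptions support the merger. For usual care, "the study team assumes similar adherence rates within statin medications and diabetes medications", and likewise for knowledge, decisional conflict and satisfaction. For the aids, "the study team assumes the same impact on all of these outcomes for all decision aids". Because the patient groups may nevertheless differ, "all models will be adjusted by group", and an arm-by-group interaction will be tested.

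The next paragraph of the section names the efficacy estimator for all patient-level outcomes, continuous and dichotomous. It is a random-effects meta-analysis of differences in means or proportions, estimated by stratum and then pooled. On the stratum it says: "A stratum in terms of a matched-pair study is considered to be each pair".

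**The concern.** Call the two practices of a pair A (diabetes aid) and B (statin/aspirin aids). The pair's aid arm is A's diabetes patients plus B's statin/aspirin patients. Its usual-care arm is B's diabetes patients plus A's statin/aspirin patients. One difference in means between these two mixtures contains the aid effect and also any outcome difference between topics, multiplied by the gap in topic share between the arms.

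The adjustment sentence is meant to deal with this, but the estimator that follows has no term for group and no stratum for topic. The planned interaction test has the same difficulty, because one estimate per pair cannot give topic-specific effects. An analyst who followed the estimator paragraph literally would leave topic mix in the effect for decisional conflict, knowledge, satisfaction and adherence alike.

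**Working it through.** **The plan's own figure.** Inputs from Sample size: difference 9.8, SDs 16.9 and 14.1, ICC 0.05, 30 per clinic, 20% attrition, 80% power, two-sided 0.05.
- SD = √((16.9² + 14.1²)/2) = 15.56. Design effect = 1 + 29 × 0.05 = 2.45.
- Per arm: 2 × (15.56 × (1.960 + 0.842)/9.8)² × 2.45 ≈ 97, so 194 analysed and 194/0.8 ≈ 243 recruited.
- The stated 240 is reproduced within rounding (power 79.6%). Topic plays no part in it, so the required number does not depend on this point.

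**Topic share in each arm.** Let pA and pB be the diabetes shares of the two practices and nA and nB their analysed numbers.
- Aid arm: pA·nA / (pA·nA + (1 − pB)·nB)
- Usual care: pB·nB / (pB·nB + (1 − pA)·nA)
- Bias of the unadjusted pair difference = topic difference in outcome × (aid share − usual-care share)

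With nA = nB and d = pA − pB, the gap is d(1 − pA − pB)/(1 − d²). It is zero when pA = pB or pA + pB = 1.

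The text gives neither topic mix nor topic difference, so both are assumed. Analysed numbers start from 30 × 0.8 = 24 per practice. All patients in a practice's aid topic are taken to use the aid.

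| pA / pB | nA : nB | aid share | usual-care share | gap | bias, 5-point difference | bias, 9.8-point difference |
|---|---|---|---|---|---|---|
| 0.5 / 0.5 | 24:24 | 0.500 | 0.500 | 0 | 0 | 0 |
| 0.7 / 0.5 | 24:24 | 0.583 | 0.625 | −0.042 | −0.21 | −0.41 |
| 0.8 / 0.5 | 24:24 | 0.615 | 0.714 | −0.099 | −0.49 | −0.97 |
| 0.9 / 0.6 | 24:24 | 0.692 | 0.857 | −0.165 | −0.82 | −1.62 |
| 0.9 / 0.5 | 24:24 | 0.643 | 0.833 | −0.190 | −0.95 | −1.87 |
| 0.5 / 0.5 | 32:16 | 0.667 | 0.333 | +0.333 | 1.67 | 3.27 |
| 0.9 / 0.5 | 16:32 | 0.474 | 0.909 | −0.435 | −2.18 | −4.27 |

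**Adherence example (assumed).** With diabetes/statin splits of 20/4 and 12/12, the shares are 20/32 = 62.5% and 12/16 = 75%. A 20-point usual-care adherence gap between topics then gives 0.125 × 20 = 2.5 points in that pair.

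**Unequal aid use (assumed).** Arms are formed by use, and Training of clinicians lets a clinician decide not to use the aid with a given patient. Take 12/12 in both practices, with the statin/aspirin aid always used and the diabetes aid used in half. The aid arm is 6/18 = 33.3% diabetes and usual care is 18/30 = 60%, a gap of −0.267. The bias is −1.33, −2.61 and −5.33 for topic differences of 5, 9.8 and 20 points, although mixes and sizes are identical.

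**Adjustment within pair.** A simulation used 4 pairs, 24 per practice, ICC 0.05, a true difference of 9.8, the first, second, third and fourth mixes in the table (24:24), topic differences of 0, 5 and 9.8, and 4,000 replicates.
- Unadjusted bias followed the formula (for example −0.99 at 0.8/0.5 and 9.8 points).
- Adjusting each pair difference for topic left at most 0.06 in absolute value. Simulation error is about 2.95/√4000 ≈ 0.05.
- The SD of the estimate was 2.20 to 2.95 adjusted and 2.20 to 2.79 unadjusted. The largest increase was 2.68 to 2.86, about 7%.

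**Differences between practices.** Take the 20/4 and 12/12 pair and a practice difference of 0.3 SD = 0.3 × 15.56 = 4.67 points.
- Unadjusted, practice A supplies 20/32 = 0.625 of the aid arm and 4/16 = 0.25 of usual care: 0.375 × 4.67 = 1.75 points.
- Stratified by topic with inverse-variance weights and equal variances, the weights are 1/(1/20 + 1/12) = 7.5 and 1/(1/4 + 1/12) = 3. The net weight is (7.5 − 3)/10.5 = 0.43, giving 2.0 points.

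Topic adjustment therefore removes the topic component and leaves the practice component.

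**The case against.** A reader might infer that the adjustment is not made, or that it cannot hold under a pair-level meta-analysis. The document supports neither. It does not call the pair differences raw. It promises adjustment in all models, and Sample size also refers to adjustment for baseline values and characteristics. A pair difference can be adjusted for topic before pooling, so the paragraphs can be made compatible.

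One may add that how a covariate enters a two-stage estimator is detail for an analysis plan that is not shown. That has some force. But the article itself fixes the estimator, the quantity differenced and the stratum, and topic is absent from all three. The conflict is in what is stated, not in what is left out.

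The design also protects the estimate. Pairs are matched on size, each clinic aims for 30 patients, and both practices supply both topics. Swapping the allocation within a pair reverses the sign of the gap, so with few pairs mix and size imbalance is mostly chance. That stands, except where recruitment or aid use after allocation differs by topic; the aid-use example has the same sign in every pair.

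The absence of a topic quota should not be claimed, because Figure 2, on eligibility and assignment by arms, is not shown. Nor should one infer that the plan rests only on equal usual-care outcomes. That assumption justifies pooling, and the adjustment is offered in case it fails.

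Practice differences are no special fault of this estimator either. In an ordinary matched-pair cluster trial, the whole practice difference enters each pair.

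**Conclusion.** The point holds as an unreconciled conflict within the Analysis section: adjustment by topic is promised, and the stated efficacy estimator does not provide for it.

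If the estimator were applied as written, the bias would be zero with equal mix, equal numbers and full aid use. With full aid use and topic differences of 5 to 9.8 points, it would be about 0 to 2 points for equal-sized practices and up to about 4 points in a single pair with 2:1 analysed sizes. The target is 9.8 points. The pooled bias is a weighted average of the pair biases, which may partly cancel. Unequal aid use by topic is the route by which they would not.

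Every mix, size ratio, uptake and topic difference here is an assumption, and there is no bias if outcomes do not differ by topic. The likely size is modest, but the correction is cheap and covers every pooled outcome, so it should be made.

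**What to change.** State in the efficacy paragraph how topic enters:
- In each pair, estimate the aid-minus-usual-care difference within topic (diabetes: A minus B; statin/aspirin: B minus A) and combine the two into one pair estimate. Equivalently, use a pair difference adjusted for topic.
- Pool the pair estimates by the planned random-effects method. "A total of 8 practices will be randomized to 1) the Diabetes Medication Choice decision aid plus statin and aspirin usual care" or to the reverse arrangement, so there are four pairs. The section's count of five strata is a separate slip to correct at the same time.
- Report topic-specific estimates with intervals beside the pooled one. This also gives the interaction test something to work from.
- Say how the two topics are weighted within a pair, and do not present the change as removing differences between practices; inverse-variance weighting does not.

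The cost is a few sentences and a few lines of code, with no new data and no change to the target of 240. The downside is small pair-by-topic cells (4 patients in the example), whose separate variances would be noisy. A pooled within-pair variance, or the adjusted pair difference, avoids that. In the simulated settings the loss of precision was at most about 7% in the SD of the estimate. Topic adjustment also does not deal with selection of which patients receive the aid when arms are formed by use.

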### Study participants and eligibility criteria

***Clinical practices.*** Eligible practices are those that have prioritized chronic disease care as an area for quality improvement and have served at least 50 patients with type 2 diabetes in the 12 months prior to the eligibility assessment. ***Primary care clinicians.*** We will recruit clinicians, defined as professionals with patient healthcare responsibilities (i.e., physicians, nurse practitioners, physician assistants), from participating practices if they are providing care to adults with type 2 diabetes. ***Patients.*** We will consider eligible adult patients (≥18 years) with type 2 diabetes if they recognize the participating clinician as their main diabetes care provider, have no major barriers to provide written informed consent (e.g., severe hearing impairment, dementia), can communicate in English, and declare being available for a six-month follow-up. Furthermore, these patients should need to start, intensify, or modify their antihyperglycemic treatment. Additional criteria will be used to identify eligibility according to designated study arms (Figure 2).

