##### Outcomes measures

To assess *Effectiveness* of the decision aids (R**E**-AIM) we will measure the decisional conflict as the primary outcome and patient involvement in decision making, diabetes care processes, medication adherence, glycemic and cardiovascular risk factor control, and resource utilization as secondary outcomes, in the following way:

· *Patients’ decisional conflict*. Patients will complete, immediately after the clinical encounter with their clinician, a modified version of the Decisional Conflict Scale [15], the most commonly used outcome measure in decision aid trials [5]. These modifications entail the use of brief items that explore the quality of the deliberation process during the visit. Psychometric properties include good internal consistency, test–retest reliability, and effect sizes for responsiveness to change ranging from 0.4 to 1.2 [15,16].

· *Patients’ involvement in decision making*. We will use the OPTION scale to assess the extent to which clinicians seek to engage patients in decision making [17,18]. OPTION is a third-person observer scale and was designed for use in reviewing audio recordings of primary care visits. Our group has extended the use of this tool to video recordings with excellent inter-rater reliability (intraclass correlation coefficient >0.7) [6,19,20].

· *Patients’ knowledge*. Patients will complete a knowledge questionnaire immediately following the encounter with their clinicians, and at 3 and 6 months post-encounter. The questionnaire was developed according to prior recommendations and is similar to questionnaires used in our previous studies, addressing general knowledge about diabetes and lipid management and specific information contained in the decision aids [6,8].

· *Patients’ satisfaction*. Satisfaction with decision making will be assessed using items from the Decisional Conflict Scale [15] as well as two specific questions that require patients to assess the extent to which they would want for themselves and recommend to others similar decision support as they received during the visit. Other questionnaires exist to specifically address this domain, but our use of the Decisional Conflict Scale for this purpose reflects our effort to minimize participant burden.

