· *Patients’ quality of life*. Patients will assess their health-related quality of life prior to the clinical encounter through the use of the EuroQol EQ-5D scale in which they list their health as excellent, very good, good, fair or poor [21]. The EQ-5D has been used in primary care [22,23] and in diabetes care and diabetes trials [24,25].

· *Patients’ hemoglobin A1c, lipids, blood pressure, & body mass index.* Medical records will be the source of information about these commonly used intermediate outcome measures for diabetes [26,27].

· *Patients’ prescription drugs.* Prescription drug and billing data will be collected through pharmacy records. Patients will be asked to provide written authorization to contact their pharmacy and release this information to the investigators. We have been able to obtain complete pharmacy records for all of our participants in previous trials [6,8].

· *Patients’ adherence*. Adherence and persistence measures will be derived from patient self-report, metabolic outcomes (indirect measure), and pharmacy records. These diverse sources are necessary given the nature of medications (e.g., multiple dosing and dose adjustments, particularly of insulin, for diabetes medication) [28,29].

· *Clinicians’ satisfaction.* Clinicians will complete a brief questionnaire after each encounter where we will ask about their satisfaction regarding the discussion they had with their patient about starting a medication.

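### The only stated HbA1c analysis is a split at an unexplained 7.3, which loses information and shows no use of baseline HbA1c; its population is worded ambiguously

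*Protocol article*

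**What the plan says.** Outcomes measures lists "glycemic and cardiovascular risk factor control, and resource utilization as secondary outcomes". For HbA1c, lipids, blood pressure and body mass index it adds: "Medical records will be the source of information about these commonly used intermediate outcome measures for diabetes". The value is therefore available as a number.

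The Analysis section then states: "Within patients that had a diabetes medication discussion, HbA1c will be collected and categorized to <7.3 versus ≥7.3". It continues: "This outcome will be analyzed as described above for categorical outcomes". The method referred to is the random-effects pooling over matched pairs, in which "differences in means for continuous outcomes and in proportions for dichotomous outcomes are estimated and then pooled across strata". For HbA1c that is a difference in the proportion below 7.3. The section schedules outcomes at baseline, 3 and 6 months.

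The Sample size section expects actual power to exceed the calculated figure partly because "we will adjust for baseline values and characteristics".

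On who belongs to the diabetes topic, the eligibility section says "these patients should need to start, intensify, or modify their antihyperglycemic treatment", and then "Additional criteria will be used to identify eligibility according to designated study arms", pointing to Figure 2, which is not shown.

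**The concern.** Glycaemic control is named in the study's objectives. Cutting a continuous measurement in two discards how far each patient lies from the threshold, and the plan gives no clinical or statistical reason for this threshold. The plan already has a method for means, so the loss is avoidable.

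Baseline HbA1c usually predicts later HbA1c, and the plan relies on baseline adjustment in general terms. The pooled difference in proportions, as described, does not show where baseline HbA1c enters.

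The population is described by whether a discussion took place. If that means an event at the visit, it occurs after practices are randomised and could differ between arms. If it means a topic assigned beforehand, it could not. The text does not say which.

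With eight practices, precision is scarce. At stake is how informative the preliminary HbA1c estimate will be.

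**Working it through.** **The plan's own figure.** The article states power for the primary outcome and none for HbA1c. With SDs 16.9 and 14.1 the pooled SD is √[(16.9² + 14.1²)/2] = 15.56. The design effect is 1 + 29 × 0.05 = 2.45. Patients analysed per arm are 240 × 0.8 / 2 = 96, so the effective number is 96 / 2.45 = 39.2. A difference of 9.8 then has 79.6% power, against 80% stated. The design arithmetic reproduces, and nothing below corrects a stated number.

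**Inputs for HbA1c.**
- From the article: cut at 7.3; ICC 0.05 (stated for the primary outcome and carried over to others); 30 recruited per practice; 20% attrition, so 24 analysed per practice; 4 practices per allocation.
- Assumed: HbA1c normally distributed, SD 1.5, mean 7.3 (cut at the median), 8.0 or 8.5; half the patients in the diabetes topic, so 12 analysed per practice; for the power illustration, a true difference of 0.5 and a baseline correlation of 0.5.

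**Step 1: independent data.** The efficiency of a split relative to the mean is φ(c)² / [p(1 − p)], with c = (7.3 − mean)/SD and p the proportion below 7.3.
- Mean 7.3: c = 0, p = 0.50; 0.3989² / 0.25 = 0.637, a loss of 36%. This is the smallest possible loss.
- Mean 8.0: c = −0.467, p = 0.320; efficiency 0.588, a loss of 41%.
- Mean 8.5: c = −0.80, p = 0.212; efficiency 0.503, a loss of 50%.

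**Step 2: allow for clustering.** Splitting a clustered normal variable also lowers its ICC. The ICC of the split value is [P(both below) − p²] / [p(1 − p)], using a bivariate normal with correlation 0.05. The efficiency becomes the Step 1 value × (design effect of the mean) / (design effect of the split). With 12 per practice the design effect of the mean is 1 + 11 × 0.05 = 1.55.

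| Mean (SD 1.5) | ICC of split | Design effect of split | Efficiency | Loss, 12 per practice | Loss, 24 per practice |
|---|---|---|---|---|---|
| 7.3 | 0.032 | 1.350 | 0.637 × 1.55/1.350 = 0.73 | 27% | 21% |
| 8.0 | 0.030 | 1.325 | 0.588 × 1.55/1.325 = 0.69 | 31% | 25% |
| 8.5 | 0.026 | 1.281 | 0.503 × 1.55/1.281 = 0.61 | 39% | 32% |

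**Step 3: what this does to power (illustration).** Effective number per arm: 4 × 12 / 1.55 = 31. For a true difference of 0.5 with SD 1.5, the standardised effect is (0.5/1.5) × √(31/2) = 1.31.
- Continuous: 26% power (normal approximation, two-sided 0.05).
- Split at 7.3, mean 8.0: 1.31 × √0.69 = 1.09, about 19%.
- Continuous, baseline-adjusted: residual variance 1 − 0.5² = 0.75; 1.31 / √0.75 = 1.52, about 33%.

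The normal approximation flatters all three with so few practices. They serve only for comparison.

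**Step 4: the population wording.** Three parts of the text bear on it. The HbA1c sentence describes members by a discussion that they had. The eligibility section requires every patient to need a change in antihyperglycaemic treatment, so its visible text does not separate a diabetes group from the others, and it leaves the separating criteria to Figure 2. The Analysis section speaks of diabetes, statin and aspirin patients as groups and adjusts models for them, which treats topic as a label. The text is compatible with both readings.

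**The case against.** The strongest reply is that this is one of many secondary outcomes in a study seeking preliminary estimates, with no power claimed for HbA1c. In the illustration even the best analysis reaches only about 33% power, so no choice would settle the question. A proportion below a threshold is also easier to relate to glycaemic control. All of this stands, and it lowers the weight of the point. It does not explain the choice of 7.3 or the absence of a continuous analysis.

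A reader might infer that the analysis selects patients on a post-randomisation event. The documents do not establish that. The phrase may simply name the topic group set by the criteria in Figure 2, and limiting HbA1c to that group is sensible because statin and aspirin discussions do not target glycaemia. What stands is the ambiguity. The Analysis section separately forms arms by actual use of an aid; that is a different issue and does not show that the diabetes group itself is formed at the visit.

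A reader might also call the analysis unadjusted. The article does speak of adjusting for baseline values and of models, and how adjustment enters the pooled differences may be left to the SAP. The fair statement is that the HbA1c analysis as described shows no use of baseline HbA1c.

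Finally, a reader might take 36% as the smallest loss in this trial, or assume that half the patients are covered. The 36% floor is for independent data, and the article gives no topic split.

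**Conclusion.** The point holds at modest weight. The protocol fixes a dichotomised analysis of a continuous secondary outcome at an unexplained cut, with no continuous analysis stated and no visible use of baseline HbA1c. The loss is about 27% to 39% with 12 analysed per practice, and 21% to 32% with 24, under ICC 0.05, normality, SD 1.5 and a mean between 7.3 and 8.5. The article supplies neither that mean and SD nor the topic split behind the 12, so these are ranges under assumptions and not properties of the trial. A more lopsided split would lose more. Ignoring baseline HbA1c would forgo a further variance reduction of 25% if its correlation with follow-up is 0.5. The population wording is unclear and should be settled; bias from it is not shown.

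**What to change.** State in the Analysis section that HbA1c at 3 and 6 months is analysed as a continuous outcome adjusted for baseline HbA1c, within the matched-pair analysis and by randomised practice. Define the population as all patients assigned to the diabetes topic before the visit, whether or not a discussion is recorded. Keep the proportion below 7.3 as a supportive summary and give the reason for that value.

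The values come from medical records and follow the existing schedule, so no new data collection is needed. The cost is revised wording and slightly more analysis work. The drawback is that a mean difference is less directly tied to a control threshold, which the supportive summary covers.
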